# Objective of Clinical Study

This clinical study aims to confirm the improvement effect of clinical outcomes in Type 2 Diabetes patients using ‘Well Check’ for 24 weeks in a real clinical setting, with or without investigator-managed linkage.

## Primary Objectives

Percent change and change of HbA1c at 24 weeks compared to baseline.

## Secondary Objectives

1. Percent change and change in FPG at 6, 12, 18, and 24 weeks compared to baseline
2. Percent change and change in HbA1c at 6, 12, and 18 weeks compared to baseline
3. Proportion of subjects achieving HbA1c < 7% at 6, 12, 18, and 24 weeks compared to baseline
4. Proportion of subjects achieving HbA1c < 6.5% at 6, 12, 18, and 24 weeks compared to baseline
5. Proportion of subjects achieving therapeutic response [change in HbA1c (baseline HbA1c – HbA1c at each evaluation time point) > 0.5% or HbA1c < 7%] at 12 and 24 weeks compared to baseline
6. Change in blood pressure (systolic and diastolic) at 6, 12, 18, and 24 weeks compared to baseline
7. Change in weight and BMI at 6, 12, 18, and 24 weeks compared to baseline
8. Proportion of subjects with a reduction of 5% or more in weight and BMI at 6, 12, 18, and 24 weeks compared to baseline

## Exploratory Objectives (Exploratory Evaluation)

1. Change in lipid levels (total cholesterol, LDL-C, HDL-C, triglycerides) at 6, 12, 18, and 24 weeks compared to baseline
2. Change in liver function markers (AST, ALT, γ-GTP) at 6, 12, 18, and 24 weeks compared to baseline
3. Change in renal function markers [e-CFR, UACR, UGC (Urine Albumin to Creatinine Ratio), UGCR (Urine Glucose to Creatinine Ratio)] at 6, 12, 18, and 24 weeks compared to baseline
4. Change in body composition analyzer indicators (skeletal muscle mass, body fat mass, body fat percentage, muscle mass, waist/hip circumference, body water, intracellular water, extracellular water, extracellular water ratio, abdominal fat percentage) at 12 and 24 weeks compared to baseline
5. Change in cardiovascular disease complication risk (ASCVD risk) at 12 and 24 weeks compared to baseline

## Safety Assessment

1. Laboratory tests, vital signs, physical examination results

# Selection of Subjects

## Number of Subjects

At least 480 subjects (minimum number to ensure statistical significance considering about 20% dropouts rate)

## Rationale

Based on the pilot study results, the difference in average HbA1c between the test group and the control group after 24 weeks of using Well Check in Type 2 Diabetes patients was considered to be 0.4% (8.0% vs. 7.6%), with a standard deviation (*s*) of 1.1%. Referring to these results, the total sample size (*n*) required was estimated to be approximately 274 subjects using G*Power 3.1.9.7.

Since this study employs cluster randomization, we further adjusted the sample size calculation by incorporating the design effect to account for potential intra-cluster correlations among patients within the same clinic. We calculated the design effect using the standard formula:

$$Design effect=1+\left( m-1 \right)\times ICC$$

Referring to previous studies conducted in primary care settings for patients with type 2 diabetes [11, 12], we conservatively adopted an intraclass correlation coefficient (ICC) value of 0.02 and assumed an average cluster size (*m*) of 20 participants per center. Therefore, we calculated the resulting design effect to be 1.38, and applying this adjustment to the initial sample size estimate gives a revised total sample size of 378 participants. Finally, considering an anticipated dropout rate of approximately 20%, we adjusted the target recruitment number further to approximately 480 participants.

[figure not shown]

< Calculation for Subject Number – Based on Glycated hemoglobin>

## Inclusion Criteria

Select individuals who meet all of the following criteria:

1. Adults aged 19 to 80 years
2. Patients with Type 2 Diabetes who are currently receiving or are scheduled to receive Envlo Tab. or Envlomet SR Tab. based on the approved conditions
3. Individuals who have no difficulty using a digital healthcare smartphone application on their smartphone
4. Individuals who plan to engage in appropriate exercise and dietary therapy for blood glucose control during the clinical study period
5. Women of childbearing potential and men who agree to use appropriate contraceptive methods or have no plans for pregnancy during the observational study period

*Hormonal contraceptives, intrauterine device (IUD) or intrauterine system (IUS) implants, vasectomy, tubal ligation, double barrier methods (simultaneous use of cervical cap or diaphragm with male condom), etc.

1. Individuals who have listened to and understood the detailed explanation of the clinical study, and have voluntarily signed a written informed consent agreeing to participate in the study and to comply with subject precautions during the study period

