# Clinical Study Method

## Overall Study Design

This clinical study is designed as a primary care-based, prospective, multicenter, cluster-randomized, pragmatic clinical trial to confirm the improvement effects on blood glucose, blood pressure, and weight over 24 weeks in patients with Type 2 Diabetes when using ‘Well Check’ with or without investigator-linked management in real-world primary care settings.

Eligible subjects include patients currently being treated with Envlo Tab. or Envlomet SR Tab. for Type 2 Diabetes or those deemed eligible for such treatment by the investigator (responsible physician). Subjects must also be able to use the digital healthcare smartphone application without difficulty.

Due to the practical constraints of primary care settings, where it is challenging to manage test group and control groups separately within the same institution, cluster randomization will be used. Institutions will be randomized as either the test group [institutions managing subjects with the 'Well Check' app in conjunction with the investigator (responsible physician)] or the control group (institutions where subjects use the 'Well Check' app for self-management). The study will be conducted following this setup.

[figure not shown]

Study Subjects

Use of 'Well Check'
for Simple Self-Management

(Control Group Institutions)

Investigator
(Responsible Physician)

Use of 'Well Check'
for Integrated Management
(Study Group Institutions)

Cluster Randomization

Participating Institutions

(Primary Care Institutions)

Figure 1. Clinical Study Design

Data collection for this clinical study will be based on medical records documented during routine clinical visits. Collected data will include demographic information, physical measurements, vital signs, and laboratory test results. There are no mandatory visits, tests, or treatments specified by this study.

However, prospective data collection through follow-up visits will be conducted up to 24 weeks from the baseline registration date.

The planned time points for prospective data collection are baseline (0 days), visit 2 (6 weeks), visit 3 (12 weeks), visit 4 (18 weeks), and visit 5 (24 weeks). Visits 2 and 4 can be optionally collected based on the investigator (responsible physician)'s judgment and allow for telephone follow-ups.

[figure not shown]

Visit 1

(0 days)

Visit 2

(6±2 weeks)

Visit 3

(12±2 weeks)

Visit 4

(18±2 weeks)

Visit 5

(24±2 weeks)

Baseline

Follow-Up Visits

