   - Former Smoker: Has smoked ≥ 5 packs (100 cigarettes) in a lifetime, but no smoking in the last 30 days
   - Non-smoker: Has smoked < 5 packs (100 cigarettes) in a lifetime
2. Lifestyle Habits (Dietary Habits): Irregular meals, overeating, excessive intake of carbohydrate/sugar, excessive fat intake, excessive salt intake
3. Lifestyle Habits (Exercise Habits): Types of exercise (walking, aerobic exercise, strength training), weekly exercise frequency, exercise intensity (less than 30 minutes, up to 1 hour, long duration)
4. **Physical Measurement**

Collect weight and BMI at every visit, with BMI automatically calculated in the CRF using height and weight. Collect height once at Visit 1 (Baseline, Day 0).

1. **Vital Signs**

At every visit, the following vital signs will be collected:

- Blood pressure (systolic/diastolic)
- Pulse Rate

Blood pressure and pulse rate should be measured in a quiet environment after at least 5 minutes of rest in a chair with a backrest. The subject should refrain from smoking, alcohol, and caffeine intake for at least 30 minutes prior to measurement, if possible.

1. **Body Composition Analysis**

For the feasible institutions capable of conducting these measurements, collect the following items at Visit 1 (Baseline, Day 0), Visit 3 (Follow-up visit, 12 weeks), and Visit 5 (Close-out visit, 24 weeks).

- Body composition analyzer indices: Skeletal muscle mass, body fat mass, body fat percentage, muscle mass, waist/hip circumference, body water, intracellular water, extracellular water, extracellular water ratio, abdominal fat percentage, etc.

1. **Prior/Concomitant Medications**

For prior medications, collect information on diabetes treatments administered within 4 weeks before Visit 1 (Baseline, Day 0). For concomitant medications, collect information on all concomitant medications taken for 3 months or more during the study period after Visit 1 (Baseline, Day 0), including those for the treatment of Type 2 Diabetes.

- Drug Name (Brand Name)
- Dosage and Administration (Dose per administration, unit, frequency, route)
- Duration of Administration (Start date, end date, ongoing status)
- Purpose of Administration
- Reason for Dose Adjustment or Discontinuation (if applicable)

1. **Laboratory Tests**

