## Randomization

Due to the practical constraints of primary care settings, where it is challenging to manage test group and control groups separately within the same institution, cluster randomization will be used. Institutions will be randomized as either the test group [institutions managing subjects with the 'Well Check' app in conjunction with the investigator (responsible physician)] or the control group (institutions where subjects use the 'Well Check' app for self-management).

For cluster randomization, participating primary medical institutions will be divided into small groups based on basic characteristics [age of the treating physician (45 years and older, or younger), region (metropolitan, non-metropolitan)]. Within these small groups, the test group and control group will be randomly assigned in a 1:1 ratio using the cluster randomization method.

To ensure strict randomization, an independent person not related to this clinical study will prepare the randomization list using the Proc PLAN procedure of SAS (Ver. 9.4 or higher, SAS Institute, Cary, NC, USA). The generated randomization list will be provided to the IWRS (interactive web response system) developer. The randomization number will be verified through IWRS.

After obtaining written consent for participation in this clinical study, the subject's screening test results will be evaluated. Only those who meet the inclusion criteria and do not fall under the exclusion criteria will be assigned a Randomization Enrollment Number.

The randomization enrollment number will be given out as “AAA-RXX-YYY” and means the following.

- “AAA”: Institution identification number
- “R”: Cluster Randomization
- “XX”: Stratification identifiers [age of the treating physician (45 years and older, or younger), region (metropolitan, non-metropolitan)]

- “YYY”: Order of randomly assigned subjects

|  | Metropolitan (X1) | Non-metropolitan (X2) |
| --- | --- | --- |
| 45 years and older (1X) | 11 | 12 |
| 45 years or younger (2X) | 21 | 22 |

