### Safety Analysis Set

Subjects who meet the inclusion/exclusion criteria, have been enrolled in this study, received the investigational product at least once according to the approved indications, and have undergone safety evaluations will be included in the safety analysis set.

1. **Methods of Analysis**
2. **General Principles**

Continuous variables will be presented as descriptive statistics (number of subjects, mean, standard deviation, median, minimum, maximum), and categorical variables will be presented as frequencies and percentages. Unless otherwise specified, all tests will be two-sided with a significance level of 5%. All p-values will be reported to a maximum of three decimal places. If not exactly divisible, values will be rounded to two decimal places, rounding up at the third decimal place.

If missing data is minimal and evenly distributed, a complete-case analysis will be considered; multiple imputation methods will be employed if missing data is substantial or disproportionately distributed between groups. Sensitivity analyses will also be performed to ensure the robustness and validity of conclusions under various missing-data scenarios.

1. **Demographic and Baseline Characteristics**

For the demographic data (age, gender, etc.) and baseline characteristics of the study subjects, continuous variables will be presented as mean, standard deviation, median, minimum, and maximum values, while categorical variables will be presented as frequency and percentage.

To assess baseline comparability between intervention and control groups, standardized mean differences (SMDs) will be calculated for key baseline characteristics, including age, sex, HbA1c, BMI, and diabetes duration. Variables exhibiting significant imbalance between groups (SMD > 0.1) will be included as covariates in subsequent analyses.

1. **Efficacy Endpoints**

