### Primary Efficacy Endpoints

For the change and percent change in HbA1c, descriptive statistics will be presented at baseline and at 24 weeks. The change from baseline to 24 weeks will be analyzed using mixed-effects models or generalized estimating equations (GEE) to account explicitly for clustering effects. Patient-level covariates identified as significantly imbalanced at baseline (SMD > 0.1) will be included as fixed effects, and inter-center variability as random effects.

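### Established users and new starters of Envlo/Envlomet are enrolled together, but baseline drug status is neither a named balance variable nor a committed covariate in the HbA1c models

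*Protocol*

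**What the plan says.** Section 3.3 (Inclusion Criteria) admits "Patients with Type 2 Diabetes who are currently receiving or are scheduled to receive Envlo Tab. or Envlomet SR Tab". Section 4.1 (Overall Study Design) repeats the mix and leaves the second group to clinical judgment: "or those deemed eligible for such treatment by the investigator (responsible physician". No period on stable treatment is required before baseline.

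Clinics are allocated 1:1 within strata of "age of the treating physician (45 years and older, or younger), region (metropolitan, non-metropolitan" (section 4.5). The balance check in section 7.2 (Demographic and Baseline Characteristics) covers "key baseline characteristics, including age, sex, HbA1c, BMI, and diabetes duration". For the primary endpoint, "Patient-level covariates identified as significantly imbalanced at baseline (SMD > 0.1) will be included as fixed effects".

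The information needed to classify patients is already gathered. Section 4.4 says "For prior medications, collect information on diabetes treatments administered within 4 weeks before Visit 1 (Baseline, Day 0"), and both that section and the data-collection schedule list start dates. No analytic use of these dates is stated. Section 4.4 also lets an HbA1c from up to 4 weeks before Visit 1 serve as the baseline value.

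**The concern.** The primary endpoint is change in HbA1c from baseline to week 24. An established user's baseline already reflects the drug. A starter's baseline does not, so the change includes whatever the drug does over the next 24 weeks. Someone who began a few weeks before Visit 1 lies in between, and may have a pre-drug baseline if the earlier HbA1c result is used.

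Baseline HbA1c cannot stand in for this. Of two patients at 8.0%, one settled on the drug and one about to begin it, the second can be expected to change more. Baseline HbA1c itself enters the model only if it happens to be imbalanced.

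Two things are at stake. Clinics will differ in their share of starters, which adds between-clinic variance to a comparison resting on 24 clinics. Also, each physician delivers one known arm while judging who is eligible, so the share could drift apart by arm. Any such difference would be read as an effect of physician linkage.

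**Working it through.** **The plan's own figure.** Section 3.2 gives a difference of 0.4, SD 1.1, ICC 0.02, cluster size 20 and 20% dropout. The readable text states no power. A two-sided 5% t-test gives 274 at 85% power. The design effect is 1 + 19 × 0.02 = 1.38, and 274 × 1.38 = 378. Then 378/0.80 = 473, and 24 clinics × 20 = 480. The sample-size arithmetic is not in question.

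**Assumptions (not in the documents).** Starters fall D = 0.3 to 0.9 points more than established users. Mean starter share is p = 0.5, with between-clinic SD s = 0.10 to 0.25. About 16 patients are analysed per clinic (480 × 0.8/24), with 12 clinics per arm.

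**Chance variation: precision.**
- Planned variance of a clinic mean: 0.02 × 1.21 + 0.98 × 1.21/16 = 0.0242 + 0.0741 = 0.0983.
- SE of the arm difference: √(2 × 0.0983/12) = 0.128.
- Variance added by the starter mix: D² × [s² + (p(1−p) − s²)/16].
- D = 0.3, s = 0.10: 0.09 × (0.0100 + 0.0150) = 0.0023. The SE rises by √(1 + 0.0023/0.0983) − 1 = about 1%.
- D = 0.9, s = 0.25: 0.81 × (0.0625 + 0.0117) = 0.0601. The SE rises by √(1 + 0.0601/0.0983) − 1 = about 27%, to 0.163.

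**Chance variation: size of the gap between arms.** The SE of the difference in starter share is √(2 × [s² + (p(1−p) − s²)/16]/12).

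| s | SE of share difference | P(gap > 10 points) | P(gap > 20 points) |
|---|---|---|---|
| 0.10 | 0.065 | about 12% | about 0.2% |
| 0.25 | 0.111 | about 37% | about 7% |

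**Chance variation: error rate.** I simulated the four corner combinations of D and s with no app effect and an unadjusted clinic-level t-test, 40,000 trials each. Rejection was 4.9% to 5.1%. The chance imbalance is already in the between-clinic variance, so a model that respects clustering keeps its 5% level.

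**Systematic difference between arms.** Shift = D × difference in starter share.

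| Difference in share | D = 0.3 | D = 0.9 |
|---|---|---|
| 10 points | 0.03 (8% of 0.4) | 0.09 (22%) |
| 20 points | 0.06 (15%) | 0.18 (45%) |

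**What the imbalance rule would do.** If drug status were tabulated, shares of 0.60 and 0.40 give an SMD of 0.20/√0.24 = 0.41, and shares of 0.50 and 0.45 give about 0.10. The rule would therefore catch a large gap. It would leave the factor out when the arms happen to be close, although clinics could still vary widely within each arm and adjustment would still gain precision.

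**The case against.** Broad eligibility is a deliberate pragmatic choice. Randomization balances starter share in expectation, and the list of balance variables is open-ended, so drug status could be added and would enter the model at any sizeable imbalance. Further covariates are often named in the SAP, which is not at hand, and section 7.2 already allows subgroup analyses by subject characteristics. Starter status is a patient attribute unknown when clinics are allocated, so its absence from the strata is no fault. The 1.1 SD and 0.02 ICC may already contain some of this mix.

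Most of that stands, and it rules out several stronger readings. A reader might infer that the 5% test really runs at 12% to 21%. Those rates follow from a fixed shift of 0.10 to 0.15 points against an SE of 1.1 × √(4 × 1.38/384) = 0.132. They do not follow from chance imbalance, which leaves the error near 5% when clustering is modelled. A reader might also say that there is no balancing or adjustment at all; randomization and the open list say otherwise. Nor do the documents show that starters are untreated, since they may be adding to or switching from other agents. No effect of the drug on weight or blood pressure is given, so nothing is claimed for those endpoints.

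The objection does not remove the gap in the rule itself. The protocol fixes an adjustment rule driven by observed imbalance, and that rule commits to nothing for a predictor of change that is known in advance and already recorded.

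**Conclusion.** The concern holds as a weakness in covariate specification. It does not show that the comparison is biased.

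Under the assumptions above, the ordinary consequence is lost precision: an SE about 1% to 27% larger than with no starter mix, the upper end needing both the largest effect and the widest clinic variation. If the planning SD and ICC already include the mix, this is not a loss against the plan, but adjustment could still recover precision.

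Bias of 0.03 to 0.18 points requires starter share to differ systematically between arms by 10 to 20 points. Recruitment by physicians who know their arm makes that plausible. The documents neither show nor size it. The drug effect and starter share are assumptions throughout.

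**What to change.** From the prior-medication start dates, derive drug status at the time of the baseline HbA1c: established, recently started, or starting at or after baseline. Classify by status or intention at Visit 1, so that planned starters who never begin stay in their group. Because eligibility requires current or planned use, an eligible patient with no Envlo/Envlomet use on record at Visit 1 is a planned starter.

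State in section 7.2 that this factor always enters the primary and secondary mixed or GEE models as a fixed effect, whatever its observed SMD, and that HbA1c results will be reported by it descriptively.

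The cost is one derived variable, a sentence or two in section 7.2, and one or two degrees of freedom. Eligibility, treatment and visits do not change.

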## Exclusion Criteria

Individuals who meet any of the following exclusion criteria will be excluded from this clinical study

1. Individuals with diabetes other than Type 2 Diabetes (e.g., Type 1 Diabetes, Diabetic Ketoacidosis, Gestational Diabetes, etc.)
2. Individuals who fall under the contraindications for administration according to the approved conditions of Envlo Tab. or Envlomet SR Tab.

- Patients who have hypersensitivity or a history of hypersensitivity to any component of Envlo Tab. or Envlomet SR Tab.
- Individuals with an estimated Glomerular Filtration Rate (eGFR) less than 30 mL/min/1.73m²
- Patients with renal impairment with an eGFR less than 60 mL/min/1.73m², end-stage renal disease, or those on dialysis
- Individuals with moderate to severe hepatic impairment (AST or ALT > 3 times the upper limit of normal, Total Bilirubin > 2 times the upper limit of normal, hepatitis, or liver failure)
- Individuals classified as class III or IV according to the New York Heart Association (NYHA) classification

1. Patients who have undergone treatment with obesity medications or weight loss drugs, or other treatments (surgery, diet, etc.) leading to unstable weight within 3 months prior to the enrollment date
2. Individuals with mental incapacity
3. Pregnant or breast-feeding women
4. Individuals participating in another clinical trial and receiving investigational drugs or investigational medical devices
5. Individuals who have prior experience using the Well Check application before study enrollment
6. Individuals deemed unsuitable for participation in this clinical study based on the judgment of the investigator (responsible physician)

